### Data collection, management, and analysis

2.9

#### Data collection methods

2.9.1

All data will be collected prospectively using eCRFs designed for this trial. The reasons for withdrawal will be documented. The investigator will attempt to contact each participant at least 3 times during each follow-up window before declaring them lost for observation. The study exit form will be recorded in the eCRF. All prior data will be analyzed within the research.

#### Data management

2.9.2

All patients will receive clarifications of all the study procedures, and will be able to discuss them with the primary investigator. All patient data will be handled according to the principles of doctor–patient confidentiality, the subjects will be anonymized and analyzed with individual identifier numbers transcribed into eCRF.

#### Statistical methods

2.9.3

An intention to treat analysis will be performed. The quantitative variables will be described as means and standard deviations or as medians, interquartile range, and range, as appropriate. Categorical variables will be described in absolute numbers and percentages. The statistical analysis of the quantitative variables, with independent groups will be performed with the parametric Student *t* test, provided that its conditions for application are met. Otherwise, the nonparametric Mann–Whitney *U* test will be used. Statistical analysis for categorical variables will use the Pearson Chi-squared test or the Fisher exact test. Specifically, the above methods will be used to compare the 2 groups in terms of baseline characteristics in order to assess whether the randomization has been effective. Overall and recurrence-free survival rates will be estimated using the Kaplan–Meier method, and the log-rank test will be used to compare overall survival between the 2 groups. Differences between groups are considered significant at *P* = .05.

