#### Screening

2.3.1

If the patient assigned an elective low anterior rectal resection meets the inclusion criteria, the patient will be asked to review the informed consent form for participation in the study; a detailed explanation of the participant's obligations and rights in case of participating in the study will be provided. All interventions related to the study will be carried out only if the patient has signed the informed consent. Upon provision of the informed consent, the patient will be assigned a number of procedures aimed at assessing the patient's compliance with the eligibility criteria:

1.Sigmoidoscopy2.Tumor biopsy3.Computed tomography of the abdominal cavity and chest4.MRI of the pelvis5.Internist and anesthesiologist consults6.Oncology case conference7.Baseline assessment of the overall and cancer-specific quality of life (SF-36 and QLQ-C30 questionnaires, respectively)8.Incontinence assessment (CCIS)

Based on the results of the screening, the stage of the disease, indications and type of surgical treatment, the possibility of performing a TME, and surgical approach (laparoscopic or open) are determined.

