#### Late postoperative period

2.3.5

It is defined as the time period starting at 31st day postsurgery. At weeks 4 to 6, according to the standard protocol, the preventive stoma is closed. Also, the patient is asked to fill out the questionnaire forms SF-36, QLQ-C30, LARS, and CCIS to assess the changes in the quality of life of the patient relative to the baseline level.

Following discharge, all subjects will be required to provide 4 filled out questionnaires (SF-36, QLQ-C30, CCIS, LARS), and report their pain level using the VAS. To ensure patient compliance to protocol requirements, all subjects will be notified telephonically and/or via e-mail. If the patient is unavailable, he or she must be contacted at least 3 times within the follow-up timeframe, before considered dropped-out from the study.

All subjects are strongly advised to adhere to bland diet, and are recommended to abstain from the intake of meat and fatty meals within at least 1 month after stoma reversal. Patients are also advised to minimize the intake of NSAIDs in the absence of comorbidities requiring NSAID treatment. NOAC administration is necessary during the 1st week after surgery to minimize the risk of thrombosis.

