#### Secondary outcome measures

2.4.2

1.Severity of AL (A, B, and C): According to the grading system suggested by Rahbari et al in the aforementioned study,^[14]^ AL is classified into^[3]^ stages depending on the necessity of therapeutic or surgical intervention.Grade A: no active therapeutic intervention requiredGrade B: requires active therapeutic intervention, but manageable without relaparotomyGrade C: requires relaparotomy2.Operating time (time frame: 1 day): The duration of surgical procedure in minutes.3.Circular stapler dysfunction rate (time frame: 1 day): The rate of circular stapler inability to create a colorectal anastomosis in a way declared by the manufacturer.4.Anastomotic bleeding rate (time frame: 30 days): The rate of bleeding from the line of stapled anastomosis verified by proctoscopy.5.Reintervention rate (time frame: 6 weeks): The rate of repeat surgeries due to anastomotic leakage.6.Early postoperative complications rate (time frame: 30 days): The rate of complications in 1st 30 days after surgery, Clavien–Dindo postoperative complication grades I to V.7.The postoperative hospital stay (time frame: 1 month): The number of days from the 1st day after operation to discharge.8.Complications of defunctioning stoma (time frame: 3 months): The rate of complications related to defunctioning stoma.9.Overall quality of life (time frame: 7 days before surgery, and 1, 3, 6, and 12 months after surgery): Assessed with patient-reported questionnaire SF-36. A total score in each of 8 sections will be calculated and transformed into a 0 to 100 scale with a score of 0 equivalent to maximum disability and a score of 100 equivalent to no disability.10.Cancer-related quality of life (time frame: 7 days before surgery, and 1, 3, 6, and 12 months after surgery): Assessed with patient-reported questionnaire European Organization for Research and Treatment of Cancer (EORTC) QLQ-C30 with supplementary module EORTC QLQ-CR29. A total score in each of 4 modules (functional scale, global health status, symptom scale, colorectal cancer module) will be calculated and converted into a 0 to 100 scale. For functional scale, global health status scale, and colorectal cancer module a score of 0 is equivalent to maximum disability and a score of 100 is equivalent to no disability. For symptom scale a score of 100 is equivalent to maximum disability and a score of 0 is equivalent to no disability.11.Manifestation of LARS (time frame: 7 days before surgery, and 1, 3, 6, and 12 months after surgery): Assessed with patient-reported questionnaire LARS, total score will be calculated (minimum 0, maximum 42) for each patient and also each patient will be assigned to either “no LARS” group (total score 0–20), “minor LARS” group (total score 21–29), or “major LARS” group (total score 30–42).12.Manifestation of fecal incontinence (time frame: 7 days before surgery, and 1, 3, 6, and 12 months after surgery): Assessed with patient-reported questionnaire CCIS, total score will be calculated (minimum 0, maximum 20) for each patient, where 0 means perfect continence and 20, complete incontinence.13.Adverse events rate (time frame: 12 months): The rate of adverse events related to circular stapler usage.14.Serious adverse events rate (time frame: 12 months): The rate of serious adverse events related to circular stapler usage.

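### The only tests named for the repeated quality-of-life, LARS and CCIS scores are two-sample tests, which neither adjust for baseline nor model the visits and leave open whether raw or change scores are compared

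*Protocol article*

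**What the plan says.** Section 2.4.2 (items 9 to 12) gives the four questionnaire outcomes the same five-point schedule. For SF-36 it reads "Overall quality of life (time frame: 7 days before surgery, and 1, 3, 6, and 12 months after surgery", for LARS "Manifestation of LARS (time frame: 7 days before surgery, and 1, 3, 6, and 12 months after surgery", and for CCIS "Manifestation of fecal incontinence (time frame: 7 days before surgery, and 1, 3, 6, and 12 months after surgery". QLQ-C30 with QLQ-CR29 follows the same times.

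The scores are also fixed there. For SF-36, "A total score in each of 8 sections will be calculated and transformed into a 0 to 100 scale"; for the cancer-specific questionnaire, "A total score in each of 4 modules (functional scale, global health status, symptom scale, colorectal cancer module) will be calculated". LARS and CCIS each have one total, and LARS is also sorted into three categories.

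Section 1.2 makes the effect of stapler type on quality of life a key secondary objective. Section 2.3.5 says the postoperative forms, LARS among them, are completed "to assess the changes in the quality of life of the patient relative to the baseline level".

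Section 2.9.3 then states the method for quantitative variables: "The statistical analysis of the quantitative variables, with independent groups will be performed with the parametric Student" *t* test, or the Mann–Whitney *U* test if its conditions fail, with significance at P = .05. The one use of these tests that it spells out is the comparison of baseline characteristics.

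On baseline collection, Section 2.3.1 lists "Baseline assessment of the overall and cancer-specific quality of life (SF-36 and QLQ-C30 questionnaires, respectively") and CCIS. Section 2.7 lists the same three instruments. Neither names LARS.

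**The concern.** The stated analysis does not fit the stated data. The trial collects a baseline and four follow-up measurements per patient in order to look at change, but the only named test compares two independent groups on one variable at a time. It takes no account of how strongly the preoperative score predicts the later one, nor of the correlation between visits. Whether the variable tested is the follow-up score or the change is left open, and the two choices can give different results and different precision.

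Three things are at stake:

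- **Precision** on a key secondary objective in a trial of 77 patients per group.
- **Number of results.** Each score yields four separate results, with no visit marked as the one that counts.
- **LARS baseline.** One section schedules it and two collection lists leave it out. If it is missed, it cannot be recovered after surgery.

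**Working it through.** The plan gives no figure for the questionnaire analyses, so there is none to reproduce. The 77 per group below comes from Section 2.6.

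**Number of tests.** Scores and visits come from Section 2.4.2; follow-up visits are 1, 3, 6 and 12 months, so 4.

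| Instrument | Scores | Scores × visits |
|---|---|---|
| SF-36 | 8 | 32 |
| QLQ-C30/CR29 | 4 | 16 |
| LARS total | 1 | 4 |
| CCIS total | 1 | 4 |
| Total | 14 | 56 |

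Testing the LARS category at each visit as well would make 60. With no effect anywhere, the expected number of false positives is 56 × 0.05 = 2.8. The chance of at least one is 1 − 0.95^56 = 94% if the tests were independent, which they are not. Simulation with assumed correlations of 0.3 to 0.7 between scores and 0.5 to 0.7 between visits gives about 53% to 85%.

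**Variance.** Let ρ be the correlation between baseline and follow-up score (an assumption; the document gives none), with equal variance at both times, set to 1. The per-patient variance entering the comparison is:

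- follow-up score only: 1
- change score: 2(1 − ρ)
- baseline-adjusted (ANCOVA): 1 − ρ²

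The ratio of adjusted to follow-up-only is 1 − ρ². The ratio of adjusted to change is (1 − ρ²) / [2(1 − ρ)] = (1 + ρ)/2.

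| ρ | Adjusted vs follow-up only | Reduction | Adjusted vs change | Reduction |
|---|---|---|---|---|
| 0.3 | 0.91 | 9% | 0.65 | 35% |
| 0.5 | 0.75 | 25% | 0.75 | 25% |
| 0.7 | 0.51 | 49% | 0.85 | 15% |

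At ρ = 0.5 the saving is the same whichever variable was meant, and is worth 1/0.75 = 1.33 times the patients.

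**Power.** With 77 per group all observed, two-sided 0.05 (Section 2.9.3 does not state sidedness) and an assumed true difference of 0.4 SD:

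| ρ | Follow-up only | Change | Adjusted |
|---|---|---|---|
| 0.3 | 0.70 | 0.56 | 0.74 |
| 0.5 | 0.70 | 0.70 | 0.82 |
| 0.7 | 0.70 | 0.89 | 0.94 |

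The difference detectable with 80% power is SD factor × √(2/77) × (1.96 + 0.8416). That is 0.45 SD for follow-up only, and 0.43, 0.39 and 0.32 SD adjusted. These are single-visit calculations with complete data.

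**Baseline lists.** Section 2.4.2 schedules LARS 7 days before surgery. Sections 2.3.1 and 2.7 name SF-36, QLQ-C30 and CCIS for baseline and do not name LARS.

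**The case against.** The strongest reply is that a two-sample comparison is valid under randomisation. Chance baseline imbalance does not bias it on average, the outcomes are secondary, and the article calls its aim preliminary. A longitudinal model, a named visit and a multiplicity rule are also things an analysis plan commonly supplies. All of that stands, and it limits the severity. It does not remove the point, because the article is not silent: it names a test family, and that family is a poor match for the design it describes.

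Four stronger readings are tempting, and the document does not support them:

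- **That the baseline is discarded.** A *t* or Mann–Whitney test can be run on change scores, and Section 2.3.5 points that way. What can be said is that the tests do not adjust for baseline and that the variable tested is unspecified.
- **That patients who miss a visit are dropped.** The plan does not say so. Section 2.9.1 says data collected before a patient leaves will be analysed. A two-sample test at 12 months cannot use that patient's 1-, 3- and 6-month scores, whereas a repeated-measures model can.
- **That the QLQ-CR29 baseline would not exist.** Section 2.4.2 defines QLQ-CR29 as a supplementary module of the QLQ-C30 assessment, and the postoperative list in Section 2.3.5 also names only QLQ-C30, so the short name plausibly covers both.
- **That the LARS baseline will not be collected.** The Section 2.3.1 list is framed around eligibility, and the participant timeline (Figure 2) is not shown, although its legend includes LARS. The text supports a mismatch between lists and nothing more.

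**Conclusion.** The point holds as one of fit and precision. The named tests neither adjust for baseline nor model the repeated visits, and raw or change scores are not distinguished. Against either reading, adjustment lowers the variance: by 9% to 49% against follow-up-only and by 15% to 35% against change scores, for ρ from 0.3 to 0.7. These sizes rest on the assumed correlations, equal variances and complete data; the direction does not depend on which ρ in that range is true.

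The count of 56 tests follows from the document if the stated test is applied to every score at every visit. The key/other ranking of secondary objectives in Section 1.2 gives some order, but it names no score or visit and carries no error-rate rule. The LARS mismatch is real and small.

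None of this touches the primary noninferiority comparison. Severity is low to moderate.

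**What to change.** In Section 2.9.3, state that each questionnaire score will be analysed with a mixed model for repeated measures containing arm, visit, arm-by-visit, baseline score and baseline-by-visit. Pre-specify one contrast per score (for example at 12 months) and make the other visits supportive.

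This reduces multiplicity but does not remove it: 14 contrasts remain, with 14 × 0.05 = 0.7 expected false positives. Either label them exploratory or name one score per instrument. That leaves 4, for which the chance of at least one false positive is 1 − 0.95^4 = 18.5% if independent and unadjusted.

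Reconcile the baseline lists in Sections 2.3.1 and 2.7 with Section 2.4.2 on LARS before enrolment, since the model for LARS needs that score. Naming QLQ-CR29 in those lists would also remove any doubt.

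The cost is a few lines of analysis text and, if LARS is not already collected, one short questionnaire at a visit where others are completed. No extra patients and no change in care are needed.

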#### Primary outcome measure

2.4.1

The primary outcome measure is the difference between the 2 groups in the incidence of colorectal anastomosis leakage documented with an X-ray and/or CT scan in the time period between the LAR and stoma reversal surgery.

As proposed by the International Study Group of Rectal Cancer, AL is defined as a “defect of the intestinal wall integrity at the colorectal or coloanal anastomotic site (including suture and staple lines of neorectal reservoirs) leading to a communication between the intra- and extraluminal compartments,” or presence of “a pelvic abscess close to the anastomosis.”^[14]^ In context of primary outcome analysis only presence or absence of diagnosed AL (dichotomous aggregation method) from the day of intervention to preventive stoma reversal will be considered. The timeframe for the primary outcome measure is defined as the period between the initial surgery and stoma reversal, which usually takes place at 4 to 6 weeks after LAR, and may differ significantly between subjects due to variability of AL presentation and symptoms. Additionally, AL may be asymptomatic and discoverable only with imaging studies, which are only necessary to ensure the safety of stoma reversal surgery.

All patients undergoing LAR with stapled colorectal anastomosis formation will be treated according to intervention protocol described in the corresponding section. The patients’ status will be monitored twice a day during rounds. AL has a multifaceted clinical course and has no pathognomonic features; it may be asymptomatic and require no intervention, or it can lead to serious complications, such as peritonitis and sepsis. The clinical signs of AL include the following:

1.General1.1. Fever (≥38.0°C)1.2. Tachycardia (≥100/min)1.3. Increased respiratory rate (≥30/min)1.4. Renal insufficiency (<30 mL/h or <700 mL/d)1.5. Altered mental status (agitation/lethargy, GCS < 15)1.6. Deterioration of overall clinical condition1.7. Peritonitis (clinical signs of abdominal guarding, rebound tenderness, abdominal pain worsening with movement, etc)1.8. Sepsis (qSOFA ≥ 2)2.Local2.1. Bowel obstruction2.2. Abnormal drain content (purulent/turbid/air)2.3. Purulent or fecal vaginal discharge (rectovaginal fistula)2.4. Abdominal pain other than wound pain2.5. Fascial dehiscence3.Laboratory signs include:3.1. Leukocytosis3.2. C-reactive protein elevation

There are several ways in which AL can be diagnosed in the investigated subjects (Fig. 1).

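### Taken literally, the one rule for categorical variables sends ordered secondary outcomes to tests that ignore order and lose power against a consistent shift to worse grades (minor; one sentence fixes it)

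*Protocol article*

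**What the plan says.** The Protocol article, Statistical methods (2.9.3), divides variables into two kinds. Quantitative variables get the Student t test if its conditions are met: "Otherwise, the nonparametric Mann–Whitney *U* test will be used". For the rest: "Statistical analysis for categorical variables will use the Pearson Chi-squared test or the Fisher exact test". Ordinal variables are not mentioned, and no test is assigned by name to any secondary outcome.

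Secondary outcome measures (2.4.2) lists three outcomes with ordered categories:
- Item 1, "Severity of AL (A, B, and C". The grades rise from no active treatment, through treatment short of reopening the abdomen, to relaparotomy.
- Item 6, "The rate of complications in 1st 30 days after surgery, Clavien–Dindo postoperative complication grades I to V".
- Item 11, LARS, recorded in two ways. One is a sum score running from 0 to 42. The other is a three-level category: "also each patient will be assigned to either “no LARS” group (total score 0–20", with minor and major groups above that.

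The primary outcome is binary: Primary outcome measure (2.4.1) counts "only presence or absence of diagnosed AL (dichotomous aggregation method".

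**The concern.** The Pearson and Fisher tests give the same result if the grade labels are shuffled. A table of two arms by k grades is tested on k − 1 degrees of freedom: 2 for LARS category, 3 for no leak/A/B/C, and 5 for none plus Clavien–Dindo I to V. If the new stapler moves patients towards worse grades throughout, that is one direction of change, and the other degrees of freedom dilute it.

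The Abstract gives the safety profile of the 3-row device as what the trial will assess, and Statistical methods judges group differences at the .05 level. With 154 patients, a consistent shift to worse grades would more easily be reported as nonsignificant, and readers may take that as reassurance.

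**Working it through.** **Arm size.** Sample size (2.6) gives rates of 18% and 30%, margin 5%, α = 0.05 one-sided and power 80%. The Blackwelder formula with the 12-point difference counted in favour of the experimental arm gives

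(1.645 + 0.842)² × (0.18×0.82 + 0.30×0.70) / (0.05 + 0.12)² = 76.5, so 77 per arm and 154 in total.

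This reproduces the stated figure. (The section attaches the 30% to the 3-row device while describing a difference in its favour. That is a separate matter; only n = 77 is used here.) No power is stated for any secondary outcome.

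**Effect model.** The cumulative odds of a better grade are divided by a common odds ratio (OR). For no leak/A/B/C at 82/6/6/6% and OR 2, the odds of no leak are 0.82/0.18 = 4.556. Halved, they are 2.278, a probability of 2.278/3.278 = 0.695. The same step at the other cut points gives 69.5/9.1/10.1/11.3%. The 82% follows from the centre's 18% leak rate; the split over A, B and C is assumed. An OR of 2 is also an assumption, though close to what 30% against 18% implies: (0.30/0.70)/(0.18/0.82) = 1.95.

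**Tests.** Pearson χ² on the full table was compared with the tie-corrected Wilcoxon–Mann–Whitney test, z = (W − E)/√V. Here E = n(N+1)/2 and V = (n²/12)[(N+1) − Σ(t³ − t)/(N(N−1))], with n = 77, N = 154 and t the number of patients in each grade. Level: two-sided 5% (the document does not state sidedness for these tests).

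**Power at OR 2, assumed set 1 (4,000 replicates).**

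| Outcome, assumed % | χ² | Rank | Loss (points) |
|---|---|---|---|
| LARS 40/25/35 | 53% | 63% | 10 |
| No leak/A/B/C 82/5/7/6 | 29% | 44% | 15 |
| None/I–V 60/12/13/8/5/2 | 37% | 63% | 26 |

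**Power at OR 1.5 / 2 / 2.5, assumed set 2 (6,000 replicates).**

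| Outcome, assumed % | χ² | Rank | Loss (points) |
|---|---|---|---|
| LARS 30/25/45 | 20/51/75% | 26/61/83% | 6/10/8 |
| LARS 50/20/30 | 21/52/79% | 27/63/86% | 6/11/7 |
| No leak/A/B/C 82/6/6/6 | 11/30/52% | 17/45/70% | 6/15/18 |
| None/I–V 60/12/12/10/4/2 | 13/35/63% | 26/62/86% | 13/27/23 |

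With no difference between arms, both tests reject in 4% to 5% of set 2 replicates.

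**Where the unordered test does better (77 per arm).**
- Non-monotone LARS, 30/25/45% against 20/45/35%: χ² 65%, rank 5%.
- Equal 18% leak rates with a worse grade mix, 82/9/6/3% against 82/3/6/9%: χ² 39%, rank 6%.

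**Two comparisons that bound the gain.**
- Leakers only: 77 × 0.18 ≈ 14 per arm. With grades 50/33/17% against 17/33/50%, χ² has 49% and the rank test 58%.
- Yes/no versions at OR 2 (set 2), tested with the 2×2 χ²: any complication 55% (rank on grade 62%); any leak 44% (rank on grade 45%).

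**The case against.** A reader might infer that the plan commits these three outcomes to unordered tests. It does not say so. The link comes from one general sentence in a condensed article, and the application that the section spells out is the check of baseline balance. A full analysis plan may assign tests outcome by outcome. This stands as a limit on the point, but the rule as printed covers all categorical variables and nothing shown qualifies it.

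The cases also differ:
- **Clavien–Dindo** is worded as a rate. For any complication yes/no, chi-squared or Fisher is the right test, and the six-level loss does not arise. It arises only if grade itself is compared, which the wording leaves open.
- **LARS** also has a 0–42 score, which falls under the t test/Mann–Whitney rule. Its order is therefore already used, and only the category test is affected.
- **Leak severity** has no score to fall back on and is the clearest case. Yet a rank test on no leak/A/B/C largely repeats the primary comparison under a uniform shift (45% against 44% for any leak).

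A stronger reading, that order is given up for no benefit, is not supported. The unordered tests assume no direction and find patterns that a rank test misses. An equal leak rate with worse leaks is one such pattern, and it matters in a noninferiority trial. Proportional odds is also the model that favours the rank test, and Fisher was not simulated although some cells are sparse (2% of 77 is about 1.5 patients).

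Nor are these the trial's leading comparisons. Objectives (1.2) lists bleeding, abscess and quality of life as key secondary objectives and puts LARS among the others.

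**Conclusion.** The point holds as a minor efficiency improvement. Taken literally, the stated rule applies unordered tests to ordered grades and loses power against a consistent shift. Across OR 1.5 to 2.5 the loss is 6–11 points for LARS category, 6–18 for no leak/A/B/C and 13–27 for a six-level Clavien–Dindo scale. These sizes rest on assumed grade distributions, proportional odds, 77 per arm and a two-sided 5% level. The direction of the loss was the same in every uniform-shift scenario.

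The figures should not be read as showing that a real worsening would be found once the test is changed: at OR 1.5 the rank test itself has only 17% to 27% power. Nor should they be read as a flaw in validity. Type I error is held under both tests, no power is claimed for these outcomes, and the binary primary outcome and the sample size are unaffected.

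**What to change.** Add one sentence to Statistical methods. Leak severity (no leak, A, B, C) and Clavien–Dindo grade (none, I to V) are compared over all randomized patients with the Wilcoxon–Mann–Whitney test or a proportional-odds model giving a common odds ratio and 95% CI. LARS category is handled the same way where it is tested in addition to the 0–42 score. Chi-squared and Fisher remain for binary and nominal variables, including any complication yes/no.

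Including no leak as the lowest level avoids a comparison among about 14 leakers per arm, a subset formed after randomization, and fits the stated intention-to-treat analysis.

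State the downside: an ordinal test can miss non-monotone differences, or a changed grade mix at equal leak rates. Report the already planned counts and percentages by grade and arm beside the test so that such patterns remain visible.

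Cost: one sentence. The rank test is already in the plan, and no extra patients or data are needed.

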### Sample size

2.6

Considering that this is a noninferiority study, the sample size was calculated using 1-sided Blackweder test.^[15]^ According to published data, the incidence of colorectal anastomotic leakage formed standard DST varies from 7% to 25%.^[16]^ Colorectal AL rate after LAR with preventive stoma formation at the study center averages at 18%. The expected incidence of colorectal AL after 3-row suturing device is 30%. The purpose of this study is to obtain preliminary results demonstrating that the outcomes of colorectal anastomosis formation with a 3-row suturing device are noninferior compared to those of a 2-row suturing device. Considering that *α* = 0.05; the statistical power of the study is 80%; the patients are randomized into 2 groups with 1:1 allocation ratio; the noninferiority margin Δ = 5%, the required sample size is 154 patients (77 patients in each of the 2 groups). Thus, if there is a true difference in favor of the experimental treatment of 12% with respect to AL rate, then 154 patients are required to be 80% sure that the upper limit of a 1-sided 95% confidence interval will exclude a difference in favor of the standard group of more than 5%.

In order to conduct an interim analysis to assess the safety of 3-row suturing devices for the formation of a colorectal anastomosis, 20 patients will be included in each group. Given a 10% probability of patients leaving the study, it is necessary to recruit 22 patients in each group. Thus, a sample of 44 patients (22 in each of the 2 comparison groups) should allow for a reliable preliminary assessment of the safety and feasibility of the use of 3-row suturing devices for the formation of colorectal anastomosis.

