## Discussion

3

This is the 1st prospective randomized clinical trial comparing the efficacy and safety of 2- and 3-row-stapling techniques in LAR for rectal cancer. This study will primarily focus on short-term outcome assessment that will allow to gather preliminary information about the use of 3-row circular staplers in rectal cancer surgery.

The design of this study has certain limitations. Firstly, there is no definitive way to exclude all the preoperative and intraoperative risk factors of AL due to their large number and the presence of nonmodifiable risk factors, such as male gender, the need for preoperative chemo-/radio-/chemoradiotherapy, or tumor size. Moreover, broadening of exclusion criteria with regard to modifiable risk factors, such as tobacco use would hinder patient recruitment significantly, and thus would delay the acquisition of definite conclusions. Additionally, whether open or minimally invasive, TME ends with rectum transection below the inferior tumor margin using a linear cutter stapler followed by colorectal anastomosis formation with a circular stapler. Thus, the quality of both linear mechanical suture on the rectal stump and of the circular stapled anastomosis between the proximal colon and the distal rectal stump influence the integrity and healing rate of colorectal anastomosis. However, in the context of this study the distance of anastomosis from the anal verge is limited to LARs, which will help to achieve homogeneity of the study groups.

Another issue is the uncertainty of the definition of AL. In this protocol, we have referred to the definition of AL proposed by the International Study Group of Rectal Cancer describing it as a “communication between the intra- and extraluminal compartments owing to a defect of the integrity of the intestinal wall at that anastomosis between the colon and rectum or the colon and anus.”^[14]^ Because there are numerous definitions of AL, diagnostic approaches vary greatly between different studies. However, the algorithm of AL diagnosis outlined in this paper allows to detect both clinically significant and asymptomatic forms of AL ensuring adequate primary outcome assessment.

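### Section 2.9.3 judges the randomization by P values on baseline characteristics, which can show neither that it worked nor that it failed

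*Protocol article*

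**What the plan says.** Section 2.9.3 (Statistical methods) lists the t test or Mann–Whitney test for quantitative variables and says "Statistical analysis for categorical variables will use the Pearson Chi-squared test or the Fisher exact test". It then gives these tests a particular task: to "compare the 2 groups in terms of baseline characteristics in order to assess whether the randomization has been effective". The threshold is general: "Differences between groups are considered significant at" P = .05, with sidedness not stated. The section does not say how many baseline variables will be tested, or what follows from a significant or non-significant result.

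Three other places bear on the point. Section 2.6 (Sample size) says "the required sample size is 154 patients (77 patients in each of the 2 groups"). Section 2.8.1 (Allocation) describes fixed block randomization and names no stratification factor. Section 3 (Discussion) concedes that not all leak risk factors can be excluded and mentions "the presence of nonmodifiable risk factors, such as male gender, the need for preoperative chemo-/radio-/chemoradiotherapy, or tumor size".

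**The concern.** A test of a baseline difference has as its null hypothesis that the difference arose by chance. When allocation follows a genuine random sequence, that null is true by construction, so the test says nothing about whether randomization worked. Reading the P value as a verdict invites two mistakes. A correctly randomized trial may be called ineffectively randomized because one of several variables fell below .05. A trial with a sizeable imbalance in a leak risk factor may be called well randomized because its P value was just above .05. A P value measures how surprising a difference is. It does not measure how much that difference matters for leakage, which is what a reader of a noninferiority result with a 5-point margin needs to know.

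**Working it through.** **Inputs from the protocol.** 77 per group, margin 5 points, one-sided alpha 0.05, 80% power and leak rates of 18% and 30% (section 2.6); baseline threshold P = .05 (section 2.9.3), taken as two-sided. **Assumed, because the protocol gives no figures:** prevalence of the risk factors (10% to 60% shown), their effect on leakage (risk ratio 2) and the number of baseline variables (5 or 10).

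**1. The plan's own sample size.** For a 12-point benefit and a 5-point margin:

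n = (1.645 + 0.842)² × (0.30×0.70 + 0.18×0.82) / (0.12 + 0.05)² = 6.183 × 0.3576 / 0.0289 = 76.5, that is 77 per group and 154 in total.

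This matches section 2.6 when the lower leak rate belongs to the experimental device. How that section labels its two rates is a separate matter. Here only n = 77 is needed.

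**2. False alarms when randomization is sound.** For k independent tests at .05, P(at least one significant) = 1 − 0.95^k.
- k = 5: 23%
- k = 10: 40%

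Positive correlation between variables, or the conservative Fisher test, lowers these figures.

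**3. Realised gaps that the test passes.** With pooled prevalence p, Pearson chi-squared flags a realised gap only above about 1.96 × √(p(1−p) × 2/77).

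| Pooled prevalence | Smallest gap flagged |
|---|---|
| 10% | 9.5 points |
| 20% | 12.6 points |
| 30% | 14.5 points |
| 40% | 15.5 points |
| 50% | 15.8 points |

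The table is symmetric about 50%. A 15-point gap therefore passes at roughly 40–60% prevalence and is flagged at about 30% or below, or 70% or above. Actual counts:

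| Counts | Gap | Chi-squared P | Fisher P |
|---|---|---|---|
| 45/77 vs 33/77 | 15.6 points | .053 | .076 |
| 31/77 vs 20/77 | 14.3 points | .060 | .086 |
| 58/77 vs 46/77 | 15.6 points | .039 | .058 |
| 19/77 vs 8/77 | 14.3 points | .020 | .033 |

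Gaps of the same size get different verdicts according to prevalence. In the third row the verdict also depends on which of the two permitted tests is used.

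**4. What a passed gap does to the leak difference.** With overall leakage 18%, prevalence p and risk ratio RR, leakage without the factor is 0.18 / (1 − p + p×RR). A 15-point gap shifts the leak difference by 0.15 × that rate × (RR − 1).
- p = 0.4, RR = 2: 0.15 × 0.1286 = 1.9 points
- p = 0.5, RR = 2: 0.15 × 0.120 = 1.8 points
- p = 0.6, RR = 2: 0.15 × 0.1125 = 1.7 points

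That is a little over a third of the 5-point margin in the trial where it happens, in either direction.

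**5. Effect over all randomizations.** In simulation with the device truly 5 points worse, a one-sided 95% upper limit from the unadjusted difference fell below the margin in 5.0–5.2% of trials. A limit from a stratum-weighted difference did so in 5.3–5.4%. Both are close to the nominal 5%.

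**The case against.** The strongest reply is that no consequence hangs on these tests. Section 2.9.3 says they assess the randomization. It does not say that a result changes the population, the analysis or the conclusion, and it already plans descriptive summaries. On this view the defect is one clause and a column of P values. That largely stands, and it limits the seriousness of the point. It does not remove it, because the clause states an inference that the tests cannot support.

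Three stronger readings are tempting, and the document does not support them.

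- **That the tests miss about half of 15-point imbalances.** Power near one half is power against a true population difference, which sound randomization rules out. A realised gap is either flagged or not, depending on prevalence: 58/77 against 46/77, close to 75% against 60%, is flagged by chi-squared at P = .039.
- **That the error rate of the noninferiority conclusion is inflated.** It is nominal over all randomizations (step 5). Rates of 7.6% to 11.6% appear only within trials where the control group has a non-significant excess of at least 10 points of the factor, about 9% of trials at an assumed 50% prevalence, with an assumed risk ratio of 2 or 3.
- **That nothing in the plan corrects for imbalance.** The protocol article states no adjusted leak analysis, but one may stand in the statistical analysis plan, which is not shown. Its absence here is not a fault.

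**Conclusion.** The point holds as a wrong stated inference. Baseline significance tests at P = .05 cannot establish whether the randomization was effective. Under correct allocation they give at least one false alarm in 23% of trials with 5 independent variables and 40% with 10. At 77 per group, chi-squared leaves unflagged a realised gap of about 15 points in a factor of roughly 40–60% prevalence. With a risk ratio of 2 and 18% leakage, such a gap moves the leak difference by nearly 2 points against a 5-point margin in that trial. The number of variables, the prevalences and the risk ratio are assumptions. The logical fault does not depend on them; its size does. The unadjusted leak comparison is valid on average, so the passage should be corrected, but the primary result is not undermined.

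**What to change.** In section 2.9.3:

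1. Delete the clause on whether randomization was effective, and the baseline P values with it.
2. Present baseline characteristics by group with the descriptive summaries the section already lists.
3. Judge the integrity of randomization by comparing the allocations given with the computer-generated sequence.
4. Prespecify, whatever balance is observed, an adjusted leak risk difference with the "upper limit of a 1-sided 95% confidence interval" that section 2.6 already refers to, set against the 5-point margin. Obtain it by standardization from a logistic model or by stratum weighting. Adjust for the factors that section 3 names: sex, preoperative therapy and tumor size. Report it beside the unadjusted difference and state in advance which of the two carries the conclusion. If the statistical analysis plan already contains such an analysis, a reference to it is enough.

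The cost is a wording change and one model, with no new patients or procedures, since these factors come from routine history and imaging. There are two small drawbacks. Leak events will be few: 154 × 0.18 ≈ 28, or 77 × 0.30 + 77 × 0.18 ≈ 37, so adjustment should stay at about three factors. The adjusted limit may also run slightly above nominal, at about 5.3% against 5% in simulation.
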